### **2.2.2 Descriptive Outcomes**

- 1) Proportion of subjects who are prescribed oral anticoagulation at the following time points:
  - i. within the first 30 days after randomization
- 2) Proportion of subjects with cumulative AF/AFL lasting for  $\geq 6$  minutes at the following time points:
  - i. within the first 30 days after randomization
  - ii. between 31 days and the last follow-up date
- 3) Proportion of subjects with detection of at least 1 episode of AF/AFL lasting for  $\geq 30$  seconds:
  - i. within the first 30 days after randomization
- 4) Proportion of subjects with detection of at least 1 episode of AF/AFL lasting for  $\geq 6$  minutes on a continuous basis at the following time points:
  - i. within the first 30 days after randomization
  - ii. between 31 days and the last follow-up date
- 5) Proportion of subjects with detection of at least 1 episode of AF/AFL lasting for  $\geq 6$  hours on a continuous basis at the following time points:
  - i. within the first 30 days after randomization
  - ii. between 31 days and the last follow-up date
- 6) Proportion of subjects with detection of at least 1 episode of AF/AFL lasting for  $\geq 24$  hours on a continuous basis at the following time points:
  - i. within the first 30 days after randomization
  - ii. between 31 days and the last follow-up date
- 7) For each subject, the total number of AF/AFL episodes lasting for  $\geq 6$  minutes on a continuous basis at the following time points:
  - i. within the first 30 days after randomization
  - ii. between 31 days and the last follow-up date

- 8) For each subject, the total number of AF/AFL episodes lasting for  $\geq 6$  hours on a continuous basis at the following time points:
  - i. within the first 30 days after randomization
  - ii. between 31 days and the last follow-up date
- 9) For each subject, the total number of AF/AFL episodes lasting for  $\geq 24$  hours on a continuous basis at the following time points:
  - i. within the first 30 days after randomization
  - ii. between 31 days and the last follow-up date
- 10) Proportion of subjects with at least one 12-lead ECG demonstrating AF/AFL at the following time points:
  - i. within the first 30 days after randomization
  - ii. between 31 days and the last follow-up date
- 11) Proportion of subjects who underwent non-protocol mandated continuous cardiac rhythm Holter monitoring and/or event recorders at the following time points:
  - i. between day 31 and the last follow-up date
- 12) Histogram of compliance percentages (protocol-mandated wearable adhesive cardiac rhythm monitoring sensor use)
  - i. Within the first 30 days after randomization
  - ii. between day 31 and the last follow-up date
- 13) Daily burden of AF/AFL burden against time (Figure): This will be calculated on a per-subject basis.
  - i. within the first 30 days
  - ii. between day 31 and the last follow-up date
- 14) Cumulative burden of AF/AFL: this metric quantifies the percentage (%) of AF/AFL detected during time periods at which protocol-mandated continuous cardiac rhythm monitoring is performed (AF/AFL burden (%) = Cumulative duration of AF/AFL detected  $\div$  Total amount of time during which protocol-mandated cardiac rhythm monitoring was performed). This will be calculated on a per-subject basis.
  - i. within the first 30 days after randomization
  - ii. between day 31 and last follow-up date
- 15) Number of subjects who prematurely removed protocol-mandated adhesive cardiac rhythm monitoring sensors at the following time periods:
  - i. within the first 30 days after randomization
  - ii. between day 31 and the last follow-up date

### **3. STUDY DESIGN**

#### **3.1 Study Design**

This is an open-label, two-arm RCT comparing a strategy of enhanced cardiac rhythm monitoring to usual care (control group) for detecting post-operative AF/AFL among post-cardiac surgical subjects at risk for developing post-operative atrial arrhythmias.

#### **3.2 Study Cohort**

The study cohort is consisted of randomized post-cardiac surgical subjects at high risk of stroke, defined as having a CHA2DS2-VASC score of  $\geq 4$  or a CHA2DS2-VASC score of  $\geq 2$  with additional risk factors for developing POAF/AFL. These subjects must not have a history of AF/AFL pre-operatively.

##### **3.2.1 Intent-to-Treat (ITT) Cohort**

The Intent-to-Treat (ITT) cohort will consist of all subjects who were randomized to the enhanced cardiac rhythm monitoring group or the control group. The primary analysis for outcomes is based on the ITT cohort. Analyses will be conducted on the ITT cohort according to the treatment group to which the subjects were randomized.

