## **12. Statistical Considerations**

### **12.1 Sample Size Calculation**

In this trial, the primary endpoint is the occurrence of sustained POAF/AFL, defined as a cumulative burden of  $\geq 6$  minutes or documentation with a 12-lead ECG. Based on the existing literature, the rate of POAF/AFL in the sub-acute, post-operative phase (within 1 month after surgery) was reported to be 2-5% [21-24]. For this trial, we assume that the rate of AF/AFL detection in the usual care group (control group) to be 3% during the first 30 days after randomization. We seek to detect at least a 3-fold or a 7% absolute increase in the rate of POAF/AFL detection with enhanced cardiac rhythm monitoring. As such, we assume a POAF/AFL detection rate of 10% in the intervention group. A total of 388 subjects (n=194 in each arm) will be required to detect this difference with 80% power at a 2-sided alpha of 0.05. Assuming a 2% attrition rate (death, loss to follow-up, withdrawal of consent to participate), the final sample size will be **396** (n=198 in each arm).

The Steering Committee of SEARCH-AF has determined that the magnitude of the difference which this trial seeks to detect (a 3-fold or an absolute 7% increase in the rate of AF/AFL detection when compared to usual care) is clinically meaningful for the population of interest.

Randomized controlled trials evaluating the efficacy of enhanced AF/AFL detection in the cryptogenic stroke population had demonstrated comparable magnitudes in differences of the primary endpoint between the treatment and control groups. In EMBRACE, the rate of AF/AFL detection was 5 times greater (absolute difference in the rate of AF/AFL detection: 12.9%) in the enhanced monitoring group when compared to the control group over a study period of 90 days [27]. In CRYSTAL-AF, the rate of AF/AFL detection was 6 times greater than the control group by 6 months (absolute difference in the rate of AF/AFL detection: 7.5%) [28]. In both studies, an AF/AFL episode lasting  $\geq 30$  seconds was the primary endpoint. As such, we feel that the magnitude of difference which we seek to detect in SEARCH-AF is realistic and achievable.

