## 12.2 Details of Statistical Analysis

Descriptive statistics will be computed. For continuous variables, mean  $\pm$  standard deviation will be reported or median and interquartile range as appropriate. For categorical variables, counts  $\pm$  percentages will be reported.

The primary analysis will be conducted with the intent-to-treat principle. The primary outcome will be displayed in a 2 x 2 contingency table, sorted according to randomization status (intervention/control group) and the presence/absence of the primary endpoint. A contingency table stratified by the surgery type stratification factor will also be examined for homogeneity of treatment effect. The number of AF/AFL episodes will be compared by means of a Poisson regression model (or possibly zero-inflated Poisson if indicated) and the treatment effect expressed as a rate ratio with 95% CI. The proportion of patients experiencing AF/AFL lasting for 24 hours or more will be compared with a Fisher's Exact test (because numbers of events and therefore expected cell counts are expected to be low). The treatment effect will be expressed as a difference in proportions with 95% CI. The proportions of patients prescribed with oral anticoagulants will be analyzed similarly.

Since outcomes related to the device itself do not have a comparison group, they will be analyzed using only descriptive statistics (means, proportions, etc.). All remaining secondary outcomes are binary and will be compared with a Fisher's Exact test (assuming the assumptions for the chi-square test are not met) and the treatment effects will be expressed as risk differences with 95% CIs. Given the expected very low attrition rate of 2%, any missing data resulting from attrition at that rate will be insufficient to substantially alter conclusions. Nevertheless some sensitivity analyses will be considered, especially given anticipated low event rates.

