| Page 28          | Secondary Outcomes (#2)   | 
Previous wording: "Cumulative AF/AFL burden during the 14-day monitoring period (recorded by the wearable adhesive cardiac monitoring device) at <math>6\pm 1</math> months after surgery."
 
Revised wording: "Cumulative AF/AFL burden during the 14-day monitoring period (recorded by the wearable adhesive cardiac monitoring device) between day 31 and the last follow-up date."
 | Due to the COVID-19 pandemic, study visit #2 (originally planned at $6\pm 1$ months after surgery) could not be conducted at the specified time window for some of the study participants. As a result, some subjects did not undergo cardiac rhythm monitoring at $6\pm 1$ months after surgery. Therefore, wording has been revised to account for the fact that cardiac rhythm monitoring was conducted outside the $6\pm 1$ month window for some participants. |
| Page 28          | Secondary Outcomes (#3)   | 
Previous wording: "Proportion of subjects who are prescribed with oral anticoagulation at the following timepoints: (i) 45 days after discharge from cardiac surgery; (ii) <math>6\pm 1</math> months after discharge from cardiac surgery; (iii) <math>9\pm 1</math> months after discharge from cardiac surgery. "
                                                                         | Due to the COVID-19 pandemic, study visits could not be conducted at the specified time windows for some of the study participants. Therefore, wording has been revised to account for the fact that study visits and collection of outcomes during follow-up visits could have been conducted outside the pre-specified time                                                                                                                                       |

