### **2.2 Secondary Objectives**

To compare the following secondary outcomes between the enhanced cardiac rhythm monitoring group and the usual care group:

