#### **2.2.1 Secondary Outcomes**

- 1) Proportion of subjects with detection of cumulative AF/AFL lasting for  $\geq 24$  hours at the following time points:
  - i. within the first 30 days after randomization
  - ii. between day 31 and the last follow-up date
- 2) Duration of cumulative AF/AFL burden detected during the 14-day monitoring period (recorded by the wearable adhesive cardiac monitoring device) among subjects:

- i. between day 31 and the last follow-up date
- 3) Proportion of subjects who are prescribed oral anticoagulation at the following time points:
  - i. within the first 45 days after discharge from surgery
  - ii. between day 46 and the last follow-up date
- 4) Number of days during which the protocol-mandated wearable cardiac rhythm monitor sensor was worn by subjects.
  - i. within the first 30 days after randomization (note: applicable for enhanced cardiac monitoring group only)
  - ii. between day 31 and the last follow-up date
- 5) Reasons for premature removal of protocol-mandated wearable adhesive cardiac rhythm monitors by subjects.
- 6) Proportion of subjects who experienced adverse events related to the use of protocol-mandated wearable adhesive cardiac rhythm monitors at the following time points:
  - i. within the first 30 days after randomization
  - ii. between day 31 and the last follow-up date
- 7) Performance of non-protocol mandated Holter monitoring and/or event recorders during the 30-day period after randomization.
  - i. within the first 30 days after randomization
- 8) Proportion of subjects who experienced major adverse cardiac event (MACE) outcomes (ALL-cause death, myocardial infarction, ischemic stroke, non-CNS system embolism) at the following time points:
  - i. within the first 45 days after discharge from surgery
  - ii. between day 46 and the last follow-up date
- 9) Proportion of subjects with major bleeding events at the following time points:
  - i. within the first 45 days after discharge from surgery
  - ii. between day 46 and the last follow-up date
- 10) Hospitalization or emergency room visits.
  - i. within the first 45 days after hospital discharge from index cardiac surgery
  - ii. between day 46 and the last follow-up date

*(note: This secondary outcome was listed in the original clinicaltrials.gov submission dated on June 2 2016 but was not explicitly listed in the protocol).*

- 11) Proportion of subjects with cumulative AF/AFL lasting for  $\geq 6$  hours at the following time points:

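### SAP 2.2.1 lists device-related adverse events for between-arm comparison, by default on all randomized subjects, against protocol 12.2; they should be described among subjects fitted with a sensor

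*Supplement*

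**What the plan says.** SAP 2.2 introduces its list of secondary outcomes with "To compare the following secondary outcomes between the enhanced cardiac rhythm monitoring group and the usual care group". Item 6 of that list (2.2.1) is "Proportion of subjects who experienced adverse events related to the use of protocol-mandated wearable adhesive cardiac rhythm monitors", in two windows: (i) the first 30 days after randomization and (ii) day 31 to last follow-up. Item 4(i), days of sensor wear in the first 30 days, carries a note restricting it to the monitored arm. Item 6(i) carries no such note.

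SAP 3.2 defines two cohorts. For the intent-to-treat cohort of all randomized subjects, 3.2.1 says "The primary analysis for outcomes is based on the ITT cohort". The per-protocol cohort (3.2.2) is defined on the first 30 days and, in the monitored arm, requires at least 24 hours of wear. No safety or fitted-subjects set is defined. SAP 4 gives every outcome comparison an estimate, a 95% confidence interval and a p-value. SAP 4.2 names a chi-squared test for secondary proportions, where appropriate. SAP 4.3 adds adjusted logistic regression for binary secondary outcomes if there are enough events.

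Protocol v4.0, section 12.2, says: "Since outcomes related to the device itself do not have a comparison group, they will be analyzed using only descriptive statistics".

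**The concern.** The SAP is to be read with the protocol, but the two give opposite instructions for item 6 and neither says which prevails. An analyst who follows the SAP literally would produce a 30-day risk difference and p-value for device events between an arm that wears the device and an arm that does not. That p-value would carry no information on device safety.

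The denominator is a separate matter. A subject who has no sensor applied in a period cannot have a device event in it, yet stays in the all-randomized denominator as event-free. Adverse events from the monitor, together with adherence, are a stated secondary objective (protocol 2.2, objective 3), so the published rate should refer to people who were exposed.

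**Working it through.** **Arm size.** The arm size used below comes from protocol 12.1: 3% v 10%, two-sided alpha 0.05, 80% power. With pooled variance and no continuity correction, mean rate 0.065:

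n = [1.960 × √(2 × 0.065 × 0.935) + 0.842 × √(0.03 × 0.97 + 0.10 × 0.90)]² / 0.07² = (0.683 + 0.290)² / 0.0049 ≈ 194 per arm.

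194 / 0.98 = 197.96, so 198 per arm and 396 in all. The plan's figures reproduce. The point does not depend on them beyond the arm size of 198.

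**Step 1: the two instructions.** SAP 2.2 with SAP 4 prescribes comparison, interval and p-value for item 6. Protocol 12.2 prescribes description only. The SAP has a separate list for description (2.2.2), on which 4.2 plans no inferential analysis, and it puts the number of subjects removing sensors early there (item 15). Item 6 stands on the comparison list.

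**Step 2: the 30-day comparison.** Protocol 5.1 mandates no continuous monitoring of controls in the first 30 days. Item 6 counts only events from protocol-mandated monitors, so the control count is 0 of 198 by definition. With k events in the monitored arm, two-sided Fisher p = 2 × C(198,k) / C(396,k):

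| k v 0 | monitored-arm rate | Fisher p |
|---|---|---|
| 4 | 2.0% | 0.123 |
| 5 | 2.5% | 0.061 |
| 6 | 3.0% | 0.030 |

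Six events would make the comparison significant. If the true rate were 5% (assumed), six or more would occur with probability 0.93. The result would follow from who wore a device. In the adjusted model of SAP 4.3, an arm with no events leaves the treatment odds ratio without a finite maximum-likelihood estimate.

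**Step 3: the denominator.** Reported rate = rate among fitted × (1 − u), where u is the share not fitted. The documents give neither quantity. Assumed ranges:

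| u | 5% among fitted | 10% among fitted | 20% among fitted |
|---|---|---|---|
| 1% | 4.95% | 9.9% | 19.8% |
| 5% | 4.75% | 9.5% | 19.0% |
| 10% | 4.5% | 9.0% | 18.0% |
| 20% | 4.0% | 8.0% | 16.0% |

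The relative understatement equals u. For the first 30 days the nearest figure in the plan is the expected crossover of under 1% (protocol 5.14), used here as a proxy for u. Fitting is within 24 hours of randomization, and the first application is supervised in hospital (5.5, 5.6.1). The first row therefore applies. For day 31 onward the documents offer no value of u.

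**Step 4: the per-protocol cohort.** It has no rule for the period after day 30. In the monitored arm it removes anyone with under 24 hours of wear, which would include a subject who took the sensor off on day one because of a skin reaction.

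**The case against.** The strongest reply is that this is a wording conflict with little practical effect. SAP 4.2 tests only where a test is appropriate, and the SAP defers to being read with a protocol that already says device outcomes are descriptive. SAP 3.2.1 does not mention device events, so the all-randomized denominator for item 6 is an inference from the absence of any other set. Wear days, reasons for removal, compliance histograms and early-removal counts are reported beside item 6, so a reader could see substantial non-wear.

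Most of this stands as a limit on size. It does not settle the conflict: item 6 is on the comparison list although a descriptive list exists, and item 4(i) is marked as one-arm while 6(i) is not. The exposure summaries also do not state a denominator for item 6.

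Four stronger readings are tempting, and the documents do not support them:

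- **Device harm is materially understated.** Not shown. Early dilution is about 1% relative on the plan's own figures, and later dilution cannot be sized.
- **Amendment 3 proves that subjects went unmonitored late.** Its rationale for secondary outcome 2 says some subjects missed the 6±1 month window, then describes monitoring done outside that window. That may mean delay, and item 6(ii) would still capture it.
- **Four events v none would already be significant.** An uncorrected chi-squared test gives p = 0.044, but the expected event count is 2 per arm. Protocol 12.2 turns to Fisher's exact test when chi-squared assumptions fail, and that gives about 0.12.
- **The late comparison is equally void.** It is not, because both arms are due to wear the device then.

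**Conclusion.** The point holds as an unresolved conflict between SAP 2.2/4 and protocol 12.2, together with a missing exposed-subject denominator. The 30-day between-arm test is uninformative whatever the event rate, because the control value is zero by design; this needs no assumption beyond the protocol's own description of usual care. The denominator effect is negligible in the first 30 days, provided the under-1% crossover expectation is a fair proxy for subjects never fitted. After day 31 it is of unknown size. It could differ by arm, since only intervention subjects have worn a sensor before and protocol 4.4 asks subjects who stop the device to stay in follow-up, but no figure in the documents shows that it does. The primary endpoint and every efficacy comparison are unaffected. It should be corrected because a published device-safety rate and p-value depend on it.

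**What to change.** In SAP 3.2, add a device-exposed set for each monitoring period: all subjects to whom at least one protocol-mandated sensor was applied in that period, whatever the wear time.

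In SAP 2.2.1, mark item 6(i) as intervention group only, as is done for 4(i). Report it as a proportion of the exposed set with a 95% confidence interval and no between-arm test. Report item 6(ii) by arm among fitted subjects, descriptively, as protocol 12.2 states. For both windows show the number not fitted, by arm and with the reason. Exclude item 6 from the p-value and adjusted-model provisions of SAP 4, 4.2 and 4.3.

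The cost is SAP wording, using wear data already needed for item 4. No trial procedure changes. One limit should be stated in the SAP: the late fitted set is not a randomized comparison, and it may still be selected if subjects who reacted to the first patch decline the second. Restricting the denominator does not remove that selection, which is why the not-fitted counts and reasons must be shown.

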##### **3.2.2 Per-Protocol (PP) Cohort**

The Per-Protocol (PP) cohort will consist of all randomized subjects who received their allocated intervention without significant deviations in the assigned treatment during the first 30 days after randomization:

- For subjects randomized to the enhanced cardiac rhythm monitoring group, the per-protocol (PP) cohort is defined by subjects who wore the sensor for  $\geq 24$  hours within the first 30 days after randomization.
- For subjects randomized to the usual care group, the PP cohort is defined by subjects who did not wear a continuous cardiac rhythm monitor (SEEQ™ or CardioSTAT® monitor) during the first 30 days after randomization.

#### **3.3 Treatment Definition**

There are two treatment groups in the study. Patients are randomized (1:1) to receive (i) usual care (control group) or (ii) enhanced cardiac rhythm monitoring (intervention group).

## **4. STATISTICAL ANALYSIS**

Categorical data will be summarized by counts and percentages, and continuous variables by means, medians and standard deviations. All outcome comparisons will include a treatment effect estimate along with a 95% confidence interval. All outcome comparisons will include a p-value calculated using an appropriate test. The adjusted estimates of the treatment effect and their 95% confidence intervals will also be reported for all relevant outcomes. Candidate covariates will include age, sex, heart failure/left ventricular (LV) dysfunction, diabetes, hypertension, history of ischemic stroke, renal disease, chronic obstructive pulmonary disease (COPD), isolated CABG vs. valve replacement/repair ± CABG, CHA2DS2-VASC score, and left atrial diameter.

### **4.1 Primary Analysis**

The primary analysis will compare the proportions of subjects with cumulative AF/AFL lasting ≥6 minutes detected by continuous cardiac rhythm monitoring or having at least one 12-lead ECG demonstrating AF/AFL within 30 days after randomization between the 2 treatment arms (enhanced cardiac rhythm monitoring group or usual care). Difference in proportions and the 95% confidence interval will be reported. A Chi-squared test of independence will be conducted to obtain the p-value.

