## **5.5 Randomization**

After study eligibility has been confirmed and the baseline visit assessment is completed, subjects will be randomly allocated in a 1:1 ratio to the intervention arm (up to 30 days of cardiac rhythm monitoring with a wearable adhesive cardiac rhythm monitoring system, starting on the day of randomization) or to the control group (usual care). Randomization lists will be generated by computer and employ random permuted blocks. Randomization will be stratified by centre and according to the type of cardiac surgery performed: (i) isolated CABG or (ii) valve replacement or repair +/- CABG. Randomization can occur at any time between the third post-operative day and discharge.

Stratification by surgery type is felt to be important for this trial for the following reasons. First, in the published literature, subjects who undergo valve replacement or repair were more likely to develop POAF with reported incidences of up to 60% during hospitalization [7,9,16,19]. These rates are higher than those who undergo isolated CABG, in which the highest rates are typically in the range of ~40% [6-20]. Second, the case volume ratio of isolated CABG to valve surgery ( $\pm$ CABG) is in the range of 4:1. Therefore, stratification will provide balance to the proportion of subjects with isolated CABG vs. valve surgery  $\pm$  CABG in both study arms.

If a subject is randomized to the intervention group, the device will be fitted onto the subject on within 24 hours of randomization. If the subject is randomized to usual care, no formal continuous cardiac rhythm monitoring will be mandated during the first 30 days after randomization. However, subjects in the usual care group may undergo rhythm assessment (e.g. ECG, Holter monitoring, event monitoring) if there is a clinical indication to do so, as per the discretion of their treating physicians.

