**Date**

## **1. INTRODUCTION**

This statistical analysis plan (SAP) outlines the planned statistical methods for the summary and analysis of data collected within the scope of the Post-Surgical Enhanced Monitoring for Cardiac Arrhythmias and Atrial Fibrillation (SEARCH-AF) trial protocol version 4.0 dated June 30 2020.

The SAP should be read in conjunction with the study protocol and the electronic Case Report Forms (eCRFs). This version of the SAP has been developed using the final version of the protocol mentioned above and eCRFs version 8.5.11 dated September 5, 2019.

All statistical analyses will be performed using R version 3.6.2, or higher.

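### The primary chi-squared test ignores the randomization strata, at little cost in power, and leaves open a continuity correction that would take power below the stated 80%

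*Supplement*

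**What the plan says.** Protocol 5.5 (version 4.0) states: "Randomization will be stratified by centre and according to the type of cardiac surgery performed". The surgery strata are isolated CABG and valve surgery with or without CABG. The protocol justifies them by in-hospital AF rates of up to 60% after valve surgery against about 40% after CABG, and by a case mix of about 4:1.

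SAP 4.1 compares the two proportions by a difference with 95% CI, and adds: "A Chi-squared test of independence will be conducted to obtain the p-value". It mentions neither stratification factor and no continuity correction. On software, SAP section 1 says only: "All statistical analyses will be performed using R version 3.6.2, or higher".

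The strata do appear elsewhere, but not in the primary test. Protocol 12.2 plans a table by surgery type to look at homogeneity. SAP section 4 lists surgery type, but not centre, as a candidate covariate. SAP 4.3 makes the regression conditional on the number of outcomes. SAP 4.4 lists surgery type as a subgroup.

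On size, protocol 12.1 states: "A total of 388 subjects (n=194 in each arm) will be required to detect this difference with 80% power at a 2-sided alpha of 0.05".

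**The concern.** When randomization is balanced on a prognostic factor and the analysis ignores it, the standard error includes between-stratum variation that the design has already removed from the comparison. The test then rejects a little less often than its nominal 5% under the null.

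The second gap could matter more. An unqualified chi-squared test on a 2x2 table has two common forms, with and without Yates' correction, and they can fall on opposite sides of 0.05. The sample size fits one form, and the named software produces the other unless told not to. In an open-label trial that choice should be in writing before database lock.

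**Working it through.** **Inputs.** From protocol 12.1: a 3% rate under usual care; for the other arm, "we assume a POAF/AFL detection rate of 10% in the intervention group"; two-sided alpha 0.05; 80% power; 2% attrition. Allocation is 1:1 (SAP 3.3). The 4:1 surgery mix is from protocol 5.5. Stratum-specific rates are not in the documents and are assumed below.

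**1. The plan's own figure.** With pooled rate 0.065, the unstratified, uncorrected formula is

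n = [1.960·√(2·0.065·0.935) + 0.842·√(0.03·0.97 + 0.10·0.90)]² / 0.07² = (0.683 + 0.290)² / 0.0049 = 193.5, so 194 per arm.

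Then 388 / 0.98 = 395.9, so 396. Both stated figures reproduce exactly. The continuity-corrected version of the formula gives 221.2, so 222 per arm.

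**2. Power with and without the correction.** Exact enumeration of both binomial distributions at 3% and 10%:

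| Per arm | Uncorrected | Yates |
|---|---|---|
| 194 | 82.4% | 76.5% |
| 198 | 83.2% | 77.5% |

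The normal approximation tells the same story: 80.1% falls to 73.8% at 194 per arm, and the corrected value at 198 is 74.8%. With the correction, 80% exact power needs 209 per arm. Exact type I error at a common 3% rate and 194 per arm is 0.048 uncorrected and 0.022 with Yates.

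The software default is not in the documents. It was checked by running R 4.3.3, which falls within the SAP's version range: a plain `chisq.test` call on a 2x2 table returns the Yates-corrected test, and `prop.test` and `mantelhaen.test` also have `correct = TRUE`.

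**3. Can the choice change the conclusion?** Take 15 against 6 events with 194 per arm, so N = 388 and 21 events in all. The cross-product difference is (15 − 6)·194 = 1746.
- Uncorrected: 388·1746² / (194²·21·367) = 4.08, p = 0.043.
- Yates: 388·(1746 − 194)² / (194²·21·367) = 3.22, p = 0.073.
- The risk difference is 4.6 points. Its 95% CI is 0.2 to 9.1 points uncorrected. Adding 1/194 (0.5 point) on each side gives -0.4 to 9.6.

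**4. Effect of stratifying by surgery type.** Simulation with 200,000 trials per scenario, 194 per arm, a 4:1 mix, arm averages held at 3% and 10% (3% in both arms for type I error), a common treatment odds ratio within strata, and no continuity correction:

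| Assumed valve:CABG odds ratio | Power, crude | Power, CMH | Type I error, crude | Type I error, CMH |
|---|---|---|---|---|
| 1 | 82.3% | 81.9% | 4.77% | 4.77% |
| 2 | 82.6% | 82.5% | 4.73% | 4.74% |
| 3 | 82.8% | 83.1% | 4.72% | 4.76% |
| 5 | 83.1% | 84.1% | 4.60% | 4.74% |

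The power difference runs from about -0.5 to +1.0 point. The crude test is below 5% even at an odds ratio of 1, because the counts are discrete; only the gap to the CMH column comes from ignoring surgery type. The protocol's own contrast of 60% against 40% is an odds ratio of (0.6/0.4)/(0.4/0.6) = 2.25, near the second row.

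An extreme assumed case, with null rates of 4% in CABG and 20% in valve patients (40,000 replicates), gives 4.3% crude and 4.9% CMH.

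Adding 5, 8 or 12 equal-sized centres as strata, at an odds ratio of 2 and with no centre effect, gives 82.4% for CMH against 82.4-82.5% crude.

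**5. The correction within CMH.** A continuity-corrected CMH test by surgery type has power of 76.3-77.9% at 194 per arm across these scenarios. Stratifying alone does not cure the second gap.

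**6. Expected events.** 194·0.03 + 194·0.10 = 5.8 + 19.4, about 25 in total.

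**The case against.** The strongest reply is that the trial was sized for exactly the test that SAP 4.1 names. A reader might infer that leaving out the strata gives away planned power. The documents do not support that: 194 per arm comes from an unstratified, uncorrected formula, and stratifying barely moves power. A crude risk difference is also a valid estimate after stratified randomization, and slight conservatism does not endanger a positive result. This stands, and it limits the stratification part to a matter of consistency.

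A reader might also infer that the SAP commits to a Yates-corrected test. It does not: it names R, but no function or option, and the uncorrected sample size suggests that an uncorrected test was intended. This stands too. The loss of about 6 points is conditional on the default being used. The gap remains because nothing in the SAP rules that out.

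The table by surgery type, the subgroup and the adjusted model do give a view by surgery type. None of them is the primary test, and the model may not be run.

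Finally, about 25 events spread over centre-by-surgery strata would leave many strata uninformative, and the documents do not give the number of centres. That is a good reason to keep centre out of the primary strata.

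**Conclusion.** The point holds in two parts of unequal weight.

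- **Strata.** The primary analysis does not follow the randomization. The cost is small: type I error of about 4.6-4.8% under assumed valve:CABG odds ratios of 1 to 5, and 4.3% only with assumed rates of 4% and 20%. The argument for stratifying is a matching standard error. These figures rest on assumed stratum rates, and a real centre effect was not modelled.
- **Continuity correction.** This is the material part. If R's default is used, exact power is 76.5% at 194 per arm and 77.5% at 198, so the attrition allowance does not bring it back to 80%. The shortfall against a correctly sized corrected test is 15 per arm on the exact basis (209 − 194) and 28 by formula (222 − 194). If the test is run uncorrected, there is no shortfall.

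**What to change.** In SAP 4.1, before database lock:

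- Make the primary test a Cochran-Mantel-Haenszel test stratified by surgery type, and state that no continuity correction is applied.
- Report the Mantel-Haenszel risk difference with its uncorrected 95% CI.
- Keep the crude chi-squared test as supportive, with `correct = FALSE` written out for both the test and its interval.
- Add centre to the strata only in a sensitivity analysis, with small centres pooled by a rule fixed in advance.

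If the team prefers the crude test as primary, the minimum is one sentence saying that it is uncorrected and one giving the reason for not stratifying.

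The cost is a few sentences. Surgery type and centre are known for every randomized subject, and no new data or change in sample size is needed.
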